## Introduction

Osteoarthritis is the most common form of arthritis, and its prevalence is projected to increase by 75% by 2050 owing to population aging [1]. Characterized by pain, stiffness, progressive inflammation, and degeneration of articular cartilage [2], osteoarthritis imposes a substantial global socioeconomic burden [1]. As the disease advances, many patients with knee osteoarthritis require total knee arthroplasty (TKA), which is a procedure with increasing demand [1].

Patients with osteoarthritis exhibit significantly lower physical activity levels than healthy older adults [3]. In this context, prolonged TKA waiting times exacerbate inactivity, contributing to muscle weakness, functional decline [4], increased comorbidities, and poorer recovery [5]. Importantly, low preoperative functional capacity is associated with poor recovery, increased surgical complications, prolonged hospital stay, and higher readmission rates, further straining healthcare systems [6].

To mitigate these issues, clinical guidelines recommend preoperative exercise programs to improve postoperative recovery. Prehabilitation enhances physical readiness for surgery, improving their ability to tolerate surgical stress, potentially improving pain management, functional capacity, and quality of life [7]. In this regard, home-based exercise programs offer a viable alternative to in-person rehabilitation by overcoming barriers such as financial constraints and limited access [8]. Notably, supervised home-based interventions demonstrate comparable efficacy to in-person rehabilitation in improving pain and function [9].

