Patients will be excluded if they fail to attend scheduled telerehabilitation sessions or respond to WhatsApp communication. Those experiencing unexpected medical complications, such as infections or cardiac or respiratory events, will be instructed to discontinue the program and withdraw from the study. The exclusion criteria also included changes in clinical status leading to surgical contraindications or new injuries during the prehabilitation period that prevented participation in home exercises. Additionally, participants with cognitive deficits were excluded based on the Portuguese version of the Mini-Mental State Examination (MMSE), with cut-off scores of ≤20 for illiterate individuals, ≤25 for primary school level, ≤26.5 for junior high school, ≤28 for high school, and ≤29 for higher education [15].

Randomization

After the explanatory meeting, eligible participants who complete baseline assessments will be randomized using simple randomization with a 1:1 allocation ratio via Randomizer® (www.randomizer.org). The allocation sequence will be generated by an independent researcher not involved in enrollment or assessment. Allocation concealment will be ensured using sequentially numbered, opaque, sealed envelopes, which will be opened only after confirming participant eligibility.

Control group

The participants in the control group will receive an institutional educational booklet containing standard preoperative physiotherapy recommendations. The only exercise instructions before TKA provided in the booklet were as follows: “(1) Move your feet up and down 20 times (active movement while lying on a treatment table, plantar dorsiflexion) and (2) inhale deeply through your nose while raising your arms and exhale through your mouth as you lower them. Perform 20 repetitions.” Participants in the control group will only follow these institutional procedures and will not engage in a home-based program. They will be instructed to maintain their usual daily activities and adhere to the recommendations provided in the booklet.

Experimental group

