Adherence to the prehabilitation program will be assessed by calculating the percentage of completed sets compared to the total prescribed sets. This information will be recorded in the training diary and reported by the patient or a family member. The number and classification of adverse events occurring during the home-based training period will be recorded separately from hospital outcomes.

Adherence will be operationally defined as the completion of ≥75% of prescribed sessions, based on adherence rates commonly reported in the literature. A recent systematic review by Adebero et al. [7] found that most prehabilitation trials achieved adherence rates of 74% or higher, supporting the use of this threshold. This cutoff will be used to determine eligibility for per-protocol analyses evaluating intervention efficacy, while all randomized participants will be retained in the dose-response analysis, regardless of adherence level.

Hospital outcomes

Hospital outcomes will include the length of hospital stay (in days), hospital readmission rate, and number and classification of complications occurring within 30 days post-surgery. These indicators were selected to complement the biological and functional recovery metrics, offering system-level proxies for early recovery quality. Specifically, reduced length of stay may reflect improved physiological readiness for discharge, while lower readmission and complication rates may signal enhanced resilience and postoperative recovery. These data will be retrieved from patients’ medical records, which will be accessed using the registration number recorded during patient enrollment. Surgical complications will be defined as any adverse events based on the Clavien-Dindo classification [26].

Satisfaction level

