Missing data will be addressed using linear regression models to examine the dose-response relationship, including participants who did not reach the ≥75% adherence threshold as well as those who withdrew from the intervention due to comorbidities or frailty. These individuals will be retained in the analysis to reflect real-world variability.

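### The dose-response regression treats achieved exercise as its exposure and keeps patients who stopped through comorbidity or frailty, so its slope can favour exercise when exercise does nothing

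*Protocol article*

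**What the plan says.** Randomization: participants are "randomized using simple randomization with a 1:1 allocation ratio". Under Experimental group and Table 1, everyone in that arm has the same prescription, three sessions a week for eight weeks and at most 24 sessions.

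Prehabilitation adherence: achieved dose is obtained by "calculating the percentage of completed sets compared to the total prescribed sets", and the information is "recorded in the training diary and reported by the patient or a family member". Completing at least 75% of sessions qualifies a patient for the per-protocol analysis, while "all randomized participants will be retained in the dose-response analysis, regardless of adherence level".

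Results, last paragraph: missing data are to be addressed with "linear regression models to examine the dose-response relationship". These include patients below the 75% threshold "as well as those who withdrew from the intervention due to comorbidities or frailty". The reason given is: "These individuals will be retained in the analysis to reflect real-world variability".

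No covariates are attached to this regression. Strengths and limitations promises sensitivity analyses for confounders. It gives adherence, engagement and expectancy as examples and names neither frailty nor comorbidity.

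**The concern.** Because the prescription is fixed, dose within the experimental arm varies only with how much of it a patient completes. For one group the article names the cause of a low dose: comorbidity or frailty. The Introduction says that "low preoperative functional capacity is associated with poor recovery, increased surgical complications, prolonged hospital stay, and higher readmission rates". Poor health is thus a plausible common cause of low dose and bad outcome, and a regression of outcome on dose credits exercise with the better results of healthier patients. Complete data would not cure this, so the point is separate from whether the regression is a method for missing data at all.

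Readers tend to take a dose-response gradient as support for a causal effect. This is also the only analysis that the article expressly says retains everyone randomised; the efficacy analysis paired with it is per-protocol. A gradient produced by health alone could be offered as evidence for a programme that the authors hope will inform public policy.

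**Working it through.** The article gives no figure for this analysis, so there is none to reproduce. The check asks how the planned slope behaves when exercise has no effect.

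**Inputs from the article.** Target of 86 at 1:1, so 43 per arm; significance level 0.05 (two-sided assumed); linear regression on achieved dose.

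**Inputs assumed.** A share w of patients is frail (10% or 20%). Their outcome is worse by δ (0.5 or 1 SD). Frail patients complete 0-50% of the dose and others 70-100%, uniformly. The true exercise effect is zero.

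**Expected slope on outcome level, experimental arm only.** With mean doses 0.25 (frail) and 0.85 (others),

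slope = −δ × (0.85 − 0.25) × w(1 − w) / Var(D).

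For w = 0.20:
- numerator: 0.60 × 0.16 = 0.096
- Var(D) = 0.16 × 0.36 + 0.20 × 0.5²/12 + 0.80 × 0.3²/12 = 0.0576 + 0.0042 + 0.0060 = 0.0678
- slope = −0.096δ/0.0678 = −1.42δ from zero to full dose, with no effect of exercise.

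**Expected slope with controls at dose 0, w = 0.20.**
- E(D) = 0.5 × (0.20 × 0.25 + 0.80 × 0.85) = 0.365
- covariance of dose with frailty: 0.5 × 0.20 × 0.25 − 0.365 × 0.20 = −0.048
- E(D²) = 0.5 × [0.20 × (0.0625 + 0.0208) + 0.80 × (0.7225 + 0.0075)] = 0.3003
- Var(D) = 0.3003 − 0.365² = 0.167
- slope = −0.048δ/0.167 = −0.29δ.

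The bias keeps its direction but shrinks to about a fifth.

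**False-positive rates on outcome level (5,000 simulated trials per cell, nominal 5%).**

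| Frail share | Outcome shift in the frail | Experimental arm only | All randomised, controls at dose 0 |
|---|---|---|---|
| 10% | 0.5 SD | 14% | 5% |
| 10% | 1 SD | 38% | 8% |
| 20% | 0.5 SD | 22% | 9% |
| 20% | 1 SD | 63% | 16% |

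**Other dose ranges.** With frail patients at 0-40% and others at 60-100%, frail shares of 10-30% and shifts of 0.3-1 SD, the rates were 8-73% in the experimental arm and 5-28% with controls at dose 0. With no link between frailty and outcome, both stayed at about 5%. Adjusting for a correctly measured frailty indicator gave 4.5-5.7%. Comparing the arms as randomised gave 4.4-5.5%.

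**Change from baseline.** If frailty adds the same amount to CRP at baseline and later, δ cancels in the difference. With a within-patient correlation of 0.5 (assumed), the rates in the four cells of the table were about 5%, with or without controls. If frailty instead alters the course of CRP, for instance by a larger postoperative rise, inflation returns: 13-64% in the experimental arm and 6-17% in all randomised.

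**Baseline adjustment.** Adding baseline CRP alone to the dose regression in the experimental arm left false positives at up to 23% with a fixed offset and up to 74% with a trajectory effect. The comparison of randomised arms adjusted for baseline CRP stayed at 4-5% in every setting.

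**The case against.** The strongest reply is that the large figures belong to an analysis the article does not describe. Prehabilitation adherence speaks of all randomised participants, which is nearer to including controls at dose 0, and there the inflation runs from none to moderate. The primary outcome is described as a change in CRP, and a fixed frailty offset disappears from a change score. Both points stand. They limit the size but do not remove the mechanism.

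Four stronger readings are tempting, and the document does not support them:

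- That low dose is always due to ill health. The article lists low adherers without a reason and adds the frail withdrawals as a second group. Screening for contraindications to exercise also limits the frail share.
- That the article says frailty raises CRP. It links low functional capacity to recovery, complications, stay and readmission, and links CRP to osteoarthritis severity and infection. The step from frailty to CRP is an inference.
- That the regression is certainly unadjusted. The article is silent, and a fuller plan may list covariates. What it does fix is the model, the exposure, who is kept and a rationale that does not mention confounding.
- That the trial's main result is biased, or that the authors claim causation from the dose slope. The primary analysis is the group × time comparison, which does not use achieved dose, and no causal claim for the slope is made.

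Keeping the withdrawn patients is itself right. The fault lies in using their dose as an exposure, and dropping them would leave the remaining dose self-selected.

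**Conclusion.** The concern holds in limited form. Dose is not randomised, some of its variation has a stated health cause, and that cause is tied by the article to the recovery and hospital outcomes. The planned slope can therefore favour exercise when exercise has no effect.

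The size depends on choices the article leaves open. With 10-20% frail and a shift of 0.5-1 SD, the false-positive rate on outcome level is about 5-16% with controls at dose 0 and 14-63% in the experimental arm alone. On change from baseline it is nominal unless frailty also alters the CRP trajectory. Frail share, shift and dose ranges are assumptions with no source in the document. The point deserves a change to the plan, but it does not touch the primary analysis.

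**What to change.** 1. Keep all randomised patients, and base any claim about the effect of the exercise done on the arms as randomised, adjusted for baseline CRP.
2. If an effect per completed session, or at 75% or more of sessions, is wanted, use randomised arm as the instrument (two-stage least squares or complier average causal effect). State that this gives one scaled contrast between arms, not a dose-response curve. State also that it assumes the daily messages and weekly video calls, which only the experimental arm receives, act solely through the exercise done.
3. If the dose regression is kept, say how controls enter and whether levels or changes are modelled. Adjust for baseline CRP, WOMAC, BMI, age and recorded comorbidity. Report it as exploratory and non-causal, because baseline adjustment alone does not remove the bias.

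Cost: mainly wording of the analysis. CRP, WOMAC, body mass and height are already measured at baseline. Comorbidity would have to be extracted from medical records, which the article describes accessing for hospital outcomes; no frailty measure is described, so some confounding would remain. The instrumental estimate has a wider confidence interval and rests on the exclusion assumption in item 2.

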## Discussion

The primary objective of this trial is to compare the effects of an eight-week semi-supervised home-based prehabilitation program with a control group on biomarkers in patients undergoing TKA. Secondary objectives include evaluating hospital outcomes (length of stay, complications, and readmission rates) and self-reported measures such as function, pain, stiffness, and satisfaction with surgery. We hypothesize that prehabilitation will lead to better outcomes, as prior studies show that exercises improve preoperative health, enhancing surgical recovery.

While postoperative rehabilitation is well-established, patients often undergo surgery in a debilitated state owing to sedentary lifestyles, which correlates with higher complication rates and worse clinical outcomes [6]. Home-based exercise programs are effective in increasing adherence among older adults and, when implemented preoperatively, can improve function, reduce pain and stiffness, lower surgical anxiety and incidence of complications, shorten hospitalization, and improve TKA satisfaction [7].

The day before surgery and the early postoperative period are critical phases of both surgical preparation and recovery. Preoperatively, biomarkers provide key insights into systemic inflammation, nutritional status, and thromboembolic risk, aiding surgical risk stratification and complication prediction. For instance, elevated preoperative CRP levels are an independent predictor of postoperative infection in arthroplasty patients [29]. Increased CRP and IL-6 levels indicate chronic inflammation, while reduced albumin and prealbumin levels suggest poor nutritional status, potentially impairing wound healing [30]. In the early postoperative phase, biomarkers reflect tissue injury, inflammation, and the progression of recovery. CRP levels peak around the third day post-surgery, indicating the magnitude of surgical trauma [17], while IL-6 levels rise earlier, marking the acute inflammatory response [20]. Lactate levels can reveal metabolic stress and inadequate perfusion [23], while IGF-1 plays a critical role in muscle regeneration [21]. Additionally, monitoring D-dimer and fibrinogen levels is crucial for assessing thromboembolic risk [31], while the presence of myokines, such as irisin and lubricin, suggests metabolic and joint-protective adaptations [22]. Finally, hemoglobin and hematocrit levels assist in identifying anemia, and coagulation markers [32] help assess thromboembolic risk.

Osteoarthritis is characterized by progressive cartilage degeneration and inflammation [2], and exercise mitigates these effects by preserving cartilage, reducing inflammation, and maintaining subchondral bone integrity [14]. Moreover, exercise influences the biomarkers linked to surgical recovery, promotes tissue regeneration, and optimizes inflammatory and thromboembolic responses. Physical activity stimulates growth factors, such as IGF-1, enhancing muscle repair and cartilage homeostasis, while mechanical loading regulates lubricin, which is crucial for joint lubrication [22]. Exercise also reduces systemic inflammation by lowering CRP and IL-6 levels [14] and preserving albumin and prealbumin levels, which are vital for wound healing and immune function. Additionally, it improves vascular function and fibrinolytic balance, thereby reducing the risk of thromboembolism.

Although biomarkers provide valuable insights into preoperative assessment, surgical response, postoperative complications, and tissue regeneration, the impact of prehabilitation on these markers in TKA patients has not been systematically investigated. Additionally, while home-based exercise programs may offer a feasible strategy to address healthcare system demands, the current lack of standardized protocols limits their structured implementation. Clarifying these protocols through rigorous studies such as this one is an important step toward refining perioperative care approaches and potentially enhancing surgical outcomes.

Strengths and limitations

We recognized potential challenges related to adherence and digital proficiency within our target age population (50-75 years). Cognitive impairments may also influence participation. However, we anticipate that video-based interactions will enhance motivation, accountability, and social support by closely replicating in-person coaching. Evidence suggests that frequent participant contact via telephone, Internet, or personal visits improves adherence to home-based exercise programs among older adults [33]. Telecommunication difficulties between participants and researchers are expected; however, to mitigate these issues, we will provide clear instructions for video call setup and allocate sufficient time to address technical challenges within our study schedule. We anticipate that technical barriers will be most prominent at the beginning of the program and diminish as participants become more accustomed to the process. Notably, a recent Brazilian study demonstrated that WhatsApp-based audio and visual messaging was effective in delivering a six-week psychosocial intervention to older adults, even without direct support from health professionals [34].

Another methodological limitation is the single-blind design, which may introduce performance and detection bias, particularly in subjective outcomes. To mitigate these biases, all outcome assessments will follow standardized protocols and be conducted by the same team of trained evaluators across both groups. Furthermore, participants in both arms will receive uniform instructions regarding their routine daily activities between baseline and surgery, minimizing behavioral discrepancies apart from the intervention itself. While self-reported outcomes are inherently prone to bias, they are measured using validated instruments with low response bias. In addition, we will perform sensitivity analyses to explore the robustness of results by accounting for potential confounders such as adherence, engagement levels, and expectancy effects. Importantly, the trial also includes objective outcomes, such as biomarkers, length of stay, complications, and anthropometric data, which enhance the overall internal validity of the findings despite the inherent limitations of a non-blinded behavioral intervention.

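### The planned sensitivity analyses treat adherence and engagement as confounders, but both follow randomisation and adherence exists only in the exercise arm, so adjusting for them cannot test robustness

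*Protocol article*

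**What the plan says.** In the Discussion, under Strengths and limitations, the authors acknowledge possible performance and detection bias because only the data analyst is blinded. Among the mitigations they write that "we will perform sensitivity analyses to explore the robustness of results" by "accounting for potential confounders such as adherence, engagement levels, and expectancy effects".

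Four other statements in Materials and methods bear on this:

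- Prehabilitation adherence, the measure: "Adherence to the prehabilitation program will be assessed by calculating the percentage of completed sets compared to the total prescribed sets".
- Prehabilitation adherence, the threshold: "completion of ≥75% of prescribed sessions". This cutoff defines the per-protocol set.
- Control group: controls "will only follow these institutional procedures and will not engage in a home-based program". They are also told to "adhere to the recommendations provided in the booklet", but no measure of that is defined.
- Randomization: "eligible participants who complete baseline assessments will be randomized using simple randomization with a 1:1 allocation ratio".

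No measure or timing is given for engagement or expectancy.

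**The concern.** A confounder of a treatment comparison is a common cause of treatment and outcome. Randomised allocation has no such causes other than chance imbalance in variables that already exist at allocation. Adherence to the programme, and engagement with it, come afterwards and because of it. On the protocol's own rationale (exercise lowers CRP and IL-6; a dose-response relationship is to be examined) they lie on the path from allocation to outcome.

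The article presents the analysis as a check on whether results are robust in a trial where participants, data collectors and assessors know the allocation. A reader of the trial report would take a change in the arm estimate after adjustment as a sign of fragility, and no change as reassurance. Neither reading would be justified.

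**Working it through.** The document gives no figure for this analysis, so there is none to reproduce. The check sets out what an adherence-adjusted arm comparison estimates, then sizes it.

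**Step 1. What the model estimates.** Fit outcome = a + b·arm + c·adherence, with adherence 0 for every control. Only the experimental arm varies in adherence, so c is the slope within that arm. The arm coefficient is then

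b = (difference in arm means) − c × (mean adherence in the experimental arm).

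This is the experimental arm's line extrapolated to zero adherence, minus the control mean. If adherence is instead left undefined for controls, they drop out and no arm comparison remains.

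**Step 2. Collinearity.** With equal arms, mean adherence m and SD s, the variance of adherence is m²/4 between arms and s²/2 within arms. The variance inflation of the arm coefficient is 1 + m²/(2s²). For an assumed m = 0.80, m²/2 = 0.32:

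| s | Variance inflation | SE multiplier | SE multiplier, simulated |
|---|---|---|---|
| 0.10 | 1 + 0.32/0.0100 = 33.0 | 5.7 | 6.0 |
| 0.15 | 1 + 0.32/0.0225 = 15.2 | 3.9 | 4.3 |
| 0.20 | 1 + 0.32/0.0400 = 9.0 | 3.0 | 3.4 |
| 0.25 | 1 + 0.32/0.0625 = 6.1 | 2.5 | 2.9 |

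The last column comes from 4,000 simulated trials per row with 39 per arm. It is slightly larger because capping adherence at 100% reduces its spread.

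**Step 3. Direction.** From the Sample size section, used only as a scale: CRP difference 9.12 mg/L, SD 10.95, and 78/2 = 39 per arm. The unadjusted standard error is 10.95 × √(2/39) = 2.48. Three cases follow from the formula in step 1:

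- *Effect proportional to dose.* c = −9.12/m, so b = −9.12 + 9.12 = 0.
- *Effect unrelated to dose.* c = 0, so b = −9.12, with the inflated standard error.
- *No effect, but healthier patients adhere more (assumed correlation 0.4 with CRP).* c = −0.4 × 10.95/s = −4.38/s, so b = +4.38 m/s. For m = 0.75 and s = 0.10 this is +32.9 mg/L; for m = 0.60 and s = 0.25 it is +10.5 mg/L.

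Simulation (4,000 trials per setting; mean/SD of adherence 0.75/0.10, 0.75/0.20, 0.85/0.15 and 0.60/0.25) agrees:

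| Case | Unadjusted estimate; share significant | Adjusted estimate | Adjusted SE | Share significant, adjusted |
|---|---|---|---|---|
| Proportional to dose | about −9.1; about 95% | −0.4 to +0.1 | 5 to 14 | about 5% |
| Unrelated to dose | about −9.1; about 95% | about −9.2 | 5 to 14 | 10% to 42% |
| No effect, adherence prognostic | about 0; about 5% | +11 to +33 | 5 to 13 | 60% to 71% |

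In these settings the correlation of adherence with arm is 0.86 to 0.98. The 95% is for a simple two-group comparison at the cited difference, not for the planned repeated-measures analysis.

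**Step 4. Is the third case plausible here?** The missing-data paragraph at the end of Results expects some participants to leave the intervention because of comorbidities or frailty. The protocol itself therefore expects adherence to track health.

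**The case against.** The strongest reply is that the article names no model. It says only that these factors will be accounted for, in one sentence of a limitations paragraph, and a statistical analysis plan may specify something else. The sentence might refer to the per-protocol and dose-response analyses described elsewhere. It stands that the coding of controls as 0 and the regression in the working are a reading, not the protocol's text. But the sentence calls these variables confounders and gives robustness as the purpose. That points to covariate adjustment, and the per-protocol and dose-response analyses are introduced separately for other ends. Nothing in the adherence or analysis sections turns the sentence into a valid analysis, and a later plan that followed it would inherit the error.

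Four stronger readings are tempting, and the document does not support them:

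- *That adjustment necessarily removes the treatment effect.* This holds only if the effect runs through exercise dose. Otherwise the estimate is imprecise, or biased.
- *That expectancy is equally wrong.* Expectancy recorded before allocation would be a legitimate covariate. No timing is given, so no error is shown.
- *That this is the trial's safeguard against lack of blinding.* It is one of several mitigations; standardised assessments, common evaluators, uniform instructions, validated instruments and objective outcomes are listed too.
- *That the main result is compromised.* The primary CRP analysis in Results does not include adherence.

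**Conclusion.** The concern holds in a limited form. Adherence and engagement with the programme follow randomisation, and adherence is defined only for the experimental arm. Calling them confounders is wrong, and adjusting the arm comparison for them does not test its robustness. With controls at 0 the standard error rises about 2.5 to 6 times for a mean adherence of 80% and an SD of 25 to 10 points. The estimate is then removed, blurred or biased, depending on how dose and health relate to the outcome. The adherence distribution, the zero coding and the correlation of 0.4 are assumptions; the post-randomisation timing and the one-arm definition are not. Severity is minor to moderate, because no primary estimate, sample size or decision rule depends on this sentence.

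**What to change.** In Strengths and limitations, and in any analysis plan that follows it:

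1. Drop adherence and engagement as adjustment covariates.
2. Keep the comparison of all randomised participants as the reference.
3. Limit covariate-adjusted sensitivity analyses to variables measured before randomisation. Include expectancy only if it is recorded before the allocation envelope is opened.
4. If the effect of exercise actually done is wanted, report as supplementary a complier-average estimate, with randomised arm as the instrument for the proportion of prescribed sets completed. State three limits:
   - It assumes that allocation acts only through exercise done. The in-person training, weekly video calls and daily messages given to the experimental arm may strain that.
   - It needs outcomes from low adherers. The Enrollment section excludes patients who miss telerehabilitation sessions or do not respond to messages, so follow-up of these patients has to be secured.
   - Its interval is wide: wider than that of the arm comparison by roughly one over mean adherence (1/0.80 = 1.25 times at 80%).

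Items 1 to 3 cost a change of wording, plus one questionnaire before allocation if expectancy is kept. Item 4 is one further analysis using the training diaries, provided outcomes are collected regardless of adherence.
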